# An integrated behavioral treatment for improving nocturia and insomnia symptoms in older adults (MINT): study protocol for a multi-site randomized clinical trial

**DOI:** 10.1186/s13063-026-09464-2

**Published:** 2026-02-16

**Keywords:** Nocturia, Insomnia, Behavioral intervention, Older adult

## Abstract

**Background:**

Nocturia (i.e., waking to void during the primary sleep period) of two or more times per night affects nearly one-third of older adults and can have a severe impact on sleep, contributing to insomnia symptoms. Current treatment approaches for nocturia often overlook non-lower urinary tract factors that may contribute to nighttime awakenings. Nocturia management, for example, may benefit from more effective integration of cognitive behavioral therapy for insomnia (CBT-I) principles that address other factors underlying insomnia symptoms, and early evidence suggests it also reduces nocturia and the bother it causes. Because nocturia treatment crosses specialties, coordinated delivery of urological and sleep therapies is a treatment barrier. The overall purpose of this trial is to determine whether a promising coordinated, integrated behavioral, non-pharmacological, non-surgical treatment that simultaneously addresses both the urological and insomnia factors contributing to nocturia is efficacious for improving nocturia, sleep, and daytime function.

**Methods:**

This multicenter parallel-group randomized, efficacy trial compares a 5-week integrated behavioral treatment program delivered by a single interventionist (psychologist, nurse practitioner, or physician assistant) to a health education control program in adults aged 60 years or older (proposed *n* = 192) recruited from sites in Atlanta and Los Angeles, who report typically getting up to urinate two or more times per night (International Consultation on Incontinence Questionnaire-Overactive bladder [ICIQ-OAB] nocturia item) and insomnia symptoms (Insomnia Severity Index > 7). The integrated program includes components of CBT-I and pelvic floor muscle exercise-based behavioral therapy for nocturia. The primary outcome is ICIQ-OAB-measured nocturia frequency 4 months after randomization. Secondary outcomes are sleep diary-measured wake after sleep onset (mean minutes) and Insomnia Severity Index total score.

**Discussion:**

The interdisciplinary trial team has developed a program aimed at improving nocturia symptoms and overall sleep of older adults in an efficient and safe manner. The integrated behavioral program has the potential to address nocturia, which is a challenging symptom because it has many etiologies that cross multiple specialties. Findings will provide rigorous evidence of the efficacy of the integrated behavioral treatment program to reduce nocturia frequency as well as sleep disturbance in older adults.

**Trial registration:**

Clinicaltrials.gov NCT06110091, registered 10/25/2023.

## Administrative information

Note: the numbers in curly brackets in this protocol refer to SPIRIT checklist item numbers. The order of the items has been modified to group similar items (see http://www.equator-network.org/reporting-guidelines/spirit-2013-statement-defining-standard-protocol-items-for-clinical-trials/).

**Table Taba:** 

Title {1}	An integrated behavioral treatment for improving nocturia and insomnia symptoms in older adults (MINT): study protocol for a multi-site randomized clinical trial
Trial registration {2a and 2b}.	clinicaltrials.gov NCT06110091, registered 10/25/2023
Protocol version {3}	March 10, 2025 (v6)
Funding {4}	National Institute on Aging (NIA) R01AG083477; in-kind support from Department of Veterans Affairs

Role of sponsor {5c}	Several of the measures included in the study follow the requirements outlined by the National Institute on Aging (NIA)’s Clinical Research Operations & Management System (CROMS). The NIA is notified of severe adverse events and has a role in determining whether the trial may be continued. However, the funder does not have any role in other aspects of study design and collection, analysis, interpretation of data, or in writing the manuscript. This material is the result of work supported with resources and the use of facilities at the Atlanta Department of Veterans Affairs (VA) Health Care System, the Greater Los Angeles VA Health Care System. The content is solely the responsibility of the authors and does not necessarily represent the official views of the VA.

## Introduction

### Background and rationale {6a}

Nocturia is a common contributor to poor health outcomes in older adults. Nearly one-third of older adults experience two or more nightly nocturia episodes (i.e., waking to void during primary sleep period) [1, 2]. Despite the usual attribution of the symptom to benign prostate enlargement in men, the prevalence of nocturia is nearly similar among older men and women, although nocturia prevalence increases more dramatically as men age compared to women [3–5]. Nocturia is reported as one of the most bothersome lower urinary tract symptoms [6, 7]. Epidemiological studies indicate that a frequency of two or more episodes of nocturia per night, in particular, is associated with significant “bother” (as measured by its effect on health-related quality of life) and is a clinically meaningful threshold [7, 8]. Nocturia is associated with multiple negative health outcomes, including more incident falls and depression [5, 9–17].

Nocturia, like geriatric syndromes, may be conceptualized as the result of accumulated impairments in multiple systems that render individuals with these conditions vulnerable to situational challenges [18]. The risk factors include biological (e.g., genetic) [19–21], contributing, and perpetuating factors. Contributing factors include those that increase urine production (either over the 24-h period or at nighttime), bladder storage problems (e.g., obstruction, infection), mental health (e.g., depression), medical conditions (e.g., diabetes, obesity) [22], and pain that disrupts sleep. Perpetuating factors include conditioned voiding responses and patient beliefs about fluid intake that may contribute to nocturia. In the proposed model, factors that are well-known contributors to insomnia symptoms, such as excessive time in bed [23], also have a role in perpetuating nocturia and its bother. Several reports suggest that older men and women with nocturia are more likely to find nocturia to be clinically bothersome if it is complicated by poor sleep quality [9, 24]. Studies indicate that nocturia is an independent predictor of insomnia [25], with greater number of trips to the toilet predicting worse patient-reported measures of insomnia (e.g., difficulty initiating sleep and returning to sleep after awakening) as well as objective measures of insomnia (e.g., longer wake bouts, worse sleep efficiency) [24, 26].

Pharmacological treatments for nocturia have modest effects and can be problematic in older adults. These treatments for nocturia (e.g., bladder relaxants, alpha blockers, desmopressin) have either poor (e.g., bladder relaxants, dihydrotestosterone blockers) or modest effects (e.g., alpha blockers) on reducing nocturia frequency [27, 28]. Moreover, medication side effects are common (e.g., desmopressin [arginine vasopressin analog]) [29] and may not be able to be used in patients who already have accumulated impairments in multiple systems, as is common among older adults [30]. Some bladder relaxants, which are often anticholinergic drugs, frequently cause dry mouth and constipation and can lead to delirium or worsened cognition. Some alpha blockers lower blood pressure and increase the risk of orthostatic hypotension, which is a risk factor for dizziness and falls. Desmopressin is associated with significant risk of serious hyponatremia with a black box warning, particularly among older adults [31]. Surgical treatments such as transurethral resection of the prostate may have limited effect on nocturia frequency [32].

Current treatment strategies (i.e., behavioral and drug approaches) for nocturia typically focus exclusively on the bladder or pelvis [33–35], and although these treatments improve nocturia frequency, a major gap is that individuals often continue to wake at night to void even after they have been treated [36, 37]. These findings suggest that additional mechanisms that contribute to nocturia need to be targeted. Non-urinary tract perpetuating factors that contribute to insomnia are viable targets for treatment using components of cognitive behavioral therapy for insomnia (CBT-I) such as sleep restriction, stimulus control, cognitive restructuring, and relaxation training [38, 39]. Consensus group and professional society guidelines recommend assessing for sleep disorders, including insomnia, among patients with nocturia [23, 40]. Recent studies have also focused on whether treatments targeting sleep disturbance result in improved nocturia symptoms. In our work, we found that nocturia frequency independently contributes to poor sleep quality, increased wakefulness at night, and longer time-in-bed, above and beyond other known demographic variables, medical conditions, and depression [41]. In another study, members of our team found that behavioral therapy directed at nocturia symptoms in older adults resulted in modest improvements on insomnia measures (i.e., time to initiate sleep, time to return to sleep after awakening) [36]. Further work has also found that brief behavioral treatment for insomnia reduces the number of self-reported nocturnal voids recorded in sleep diaries compared to an information control in older adults with chronic insomnia (effect size 0.82) [42].

The proposed bidirectional relationship between nocturia and factors that cause insomnia symptoms [43] (and those that may have the potential to cause more disruptive or problematic nocturia) led to our development of a multicomponent, non-pharmacological, non-surgical treatment strategy targeting the perpetuating factors of nocturia and insomnia. In an earlier study, we established that a multicomponent behavioral and lifestyle intervention that addressed sleep disruption in the context of nocturia, incorporating sleep hygiene with nocturia treatments (e.g., pelvic floor muscle exercise-based urge suppression at night), was well-tolerated and feasible [37]. Moreover, behavioral therapy reduced nocturia frequency equal to or at least as much as drug therapy [36, 37, 42, 44]. This evidence of improvement in nocturia frequency was tempered by small improvement in sleep outcomes, including a non-significant change in sleep efficiency and wakefulness after sleep onset [37]. The results suggested a need to add more potent behavioral sleep components (e.g., sleep restriction) to improve treatment of nocturia in older adults.

This work led to the current randomized trial comparing an integrated, multicomponent behavioral intervention to a health education control program in adults aged ≥ 60 with concomitant nocturia and insomnia symptoms to provide rigorous evidence of the efficacy of the integrated program [38]. Informed by our recent trials and prior feasibility study (IRB#16160003), we are recruiting participants using a multi-pronged process designed to limit participant burden while yielding high levels of participation. The 5-week treatment delivered by a single interventionist, which involves an integrated nocturia and insomnia intervention (includes education, lifestyle habits management, cognitive, relaxation, and behavioral conditioning for nocturia and insomnia), addresses the bidirectional relationship between these important and common symptoms.

### Objectives {7}

#### Specific Aim 1

Determine the efficacy of the integrated nocturia and insomnia behavioral intervention program for improving nocturia frequency over 4 months in older adults with nocturia and insomnia symptoms.

##### Hypothesis 1

Compared to a control arm of health education, participants assigned to the integrated intervention program will demonstrate a greater reduction in mean nocturia frequency over 4 months.

#### Specific Aim 2

Assess the efficacy of the integrated nocturia and insomnia behavioral intervention for reducing sleep disturbance over 4 months in older adults with nocturia and insomnia symptoms.

##### Hypothesis 2

Compared to a health education control arm, participants assigned to the integrated intervention program will have greater reduction (i.e., improvement) in self-reported wake after sleep onset and Insomnia Severity Index over the 4-month follow-up period.

#### Specific Aim 3

Examine the effects of the integrated nocturia and insomnia behavioral intervention on quality of life (daytime function) related to nocturia and sleep quality over 4 months in older adults with nocturia and insomnia symptoms.

##### Hypothesis 3

Participants randomized to the integrated intervention program will report more improvement in Nocturia-Quality of Life scores and Pittsburgh Sleep Quality Index Global Score (lower scores) from baseline to post-treatment and 4-month follow-up compared to control.

### Trial design {8}

Randomized parallel group superiority trial (1:1 allocation).

## Methods: participants, interventions and outcomes

### Study setting {9}

Participant recruitment is based at two sites within the United States: The Department of Veterans Affairs (VA) Greater Los Angeles and the Atlanta VA, within the Geriatric Research, Education and Clinical Centers and respective outpatient clinics at each site. Additionally, patients are recruited from outpatient clinics at two universities affiliated with these VA centers, the University of California Los Angeles (UCLA) Health System and Emory University. Data coordination activities are based at the University of California, San Francisco (UCSF). Additional quality control for intervention (e.g., fidelity ratings) is conducted by co-investigators at the Birmingham VA and the University of Utah/Salt Lake City VA. This list of study sites is comprehensive and is also available from the corresponding author.

### Eligibility criteria {10}

Participant eligibility criteria include the following:

Inclusion criteria: 

Age ≥ 60 yearsAverage of ≥ 2 episodes per night of nocturia on the International Consultation on Incontinence Questionnaire-Overactive Bladder Module (ICIQ-OAB) questionnaireInsomnia Severity Index > 7Able to attend weekly in-person or virtual study visits

Exclusion criteria:

Presence of bipolar disorderSignificant cognitive impairment as measured by a score < 20 on the Mini-Mental State ExaminationSleep disturbance better explained by another sleep disorder such as restless legs syndrome, narcolepsy, insufficient sleep syndrome, or circadian rhythm sleep-wake disordersUntreated sleep-disordered breathing (respiratory event index ≥ 15 plus Epworth Sleepiness Scale > 10, or respiratory event index ≥ 30. Note that participants with treated sleep-disordered breathing are *not* excluded)Current urinary tract infection or hematuria (based on screening urinalysis testing)Unstable doses or recent changes (past month) in medications affecting lower urinary tract symptomsNew or recently discontinued insomnia medication within the past monthPrevious or current intensive behavioral therapy for insomnia or urinary symptomsUnstable health conditions expected to result in death or hospitalization within 3 monthsUnstable medical conditions that could contribute to nocturia or insomnia such as poorly controlled heart failure as evidenced on physical examination, poorly controlled diabetes mellitus with either hemoglobin A1c of ≥ 9.0, or chronic kidney disease (stage 4 or 5) or a potential to initiate dialysis in 3 monthsUnstable psychiatric conditions (e.g., psychosis, active alcohol/substance abuse based on history and medical records)Unstable housing situationEvidence of significant urinary retention (e.g., as measured by a residual bladder volume of ≥ 200 mL by bladder ultrasound or catheterization with 15 min of voiding)Genitourinary cancer undergoing active treatmentPelvic or colon surgery within 6 months of enrollment or onabotulinum toxin therapy for urinary symptoms within 6 months of enrollment

Interventionist eligibility criteria: The intervention protocols were designed for delivery by a clinician who may be an advanced practice practitioner (e.g., nurse practitioner or physician assistant who delivers behavioral treatment in a urology clinic) or a clinical psychologist (e.g., behavioral sleep specialist who delivers cognitive behavioral therapy for insomnia in a sleep center) and who is fully trained in the intervention protocols by the study clinician scientists. Including clinicians with diverse training and background will facilitate future dissemination, since our goal is to develop a cross-disciplinary intervention program.

### Who will take informed consent? {26a}

Research coordinators working under the supervision of clinician Site PIs, using an institutional review board (IRB)-approved process, meet (either in-person or through a video visit) with prospective participants who have undergone preliminary screening either by telephone or in-person. When a prospective participant attends the consent visit, a research staff member discusses the study details with the prospective participant and assesses their capacity to sign the informed consent forms by asking the prospective participant to recount the main purpose of the trial, risks and benefits of participation, and options if the individual no longer wishes to participate. They may sign the informed consent forms (either through e-consent platform approved by the institutions or with a wet signature). Proxy is not pursued for individuals who do not have the capacity to provide informed consent.

### Additional consent provisions for collection and use of participant data and biological specimens {26b}

No biological specimens are collected for analysis. Home sleep apnea test results that suggest sleep apnea diagnosis may be shared with the participant’s clinical team, if the participant gives the research team permission to share the results.

## Interventions

### Explanation for the choice of comparators {6b}

The integrated behavioral intervention is compared to a healthy aging education control program as an attention control condition, to address the goal of the project to establish the initial efficacy of the integrated behavioral intervention. The two programs were selected to be comparable in number of sessions, to be behavioral in nature (non-pharmacological, non-surgical), to be provided through a video visit or in-person visit over 5 visits in addition to up to 2 telephone check-in calls, to be delivered entirely (all sessions) by a single interventionist, and to have a structured format (slide presentation, binder with handouts, and “homework” between sessions).

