#### Healthy aging education control arm

Participants attend visits with the interventionist to control for time and attention, which enhances the scientific rigor of our trial. The interventionist provides a health education curriculum. The health education modules focus on brain health and include topics such physical activity, social engagement, sleep topics (e.g., changes in sleep that occur with aging, effects of poor sleep on health), medications/medical conditions, vision and hearing impairment. Brief telephone check-ins are comprised of review of health topics discussed during the sessions. Goals (e.g., physical activity, track medications daily) are established at the visits, and progress towards these goals is monitored in a workbook that mirrors the sleep/bladder diary of the integrated program but does not include items from the sleep/bladder diary because it is considered a self-monitoring intervention. Brief telephone check-ins (up to two) are conducted to discuss progress on goals previously established during the 5 content sessions.

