### Sample size {14}

Power calculations are informed by parameter assumptions derived from past clinical trials of behavioral interventions for lower urinary tract symptoms and/or sleep disorders conducted by our study team members or consultants, corroborated by trends in our previous integrated nocturia and insomnia intervention feasibility study [36, 37, 55]. We assume an average frequency of at least 16 nocturia episodes per week (~ 2.3 episodes/night) in our baseline trial population, and an average decrease in nocturia frequency of 2 episodes per week (~ 0.3 episodes/night) over 4 months in the control group, given a recent systematic review including 17 trials assessing placebo-response in studies of treatments for nocturia [56]. We also anticipate a clinically meaningful reduction in nocturia frequency (item from the ICIQ-OAB) in the integrated nocturia and insomnia intervention group of at least 7 episodes per week (~ 1 episode per night) over 4 months, leading to a between-group difference in improvement in nocturia frequency of 5 or more episodes per week (0.7 episodes/night) between the integrated nocturia and insomnia intervention and control arms. This effect size represents a meaningful threshold of improvement in nocturia frequency that can be communicated to patients and clinicians, and corresponds to a clinically meaningful improvement of greater than half a standard deviation in the mean nightly nocturia frequency given a range of potential standard deviations [56, 57]. Using an approximation of the covariance matrix of the regression coefficients of the proposed linear mixed effects models (LMMs), we estimate that a sample of 192 participants, randomized in equal proportions to the two arms, will provide > 80% power in 2-sided tests with an experiment-wise type-I error rate of 5% [58], to detect the proposed greater reduction in nocturia frequency of least 5 episodes/week (0.7 episodes/night) associated with integrated intervention versus control intervention, assuming a cumulative loss to follow-up level of less than 15% accumulated at roughly equal rates between sequential follow-up visits. The assumption of loss-to-follow-up < 15% is based on our existing integrated intervention feasibility study, as well as prior trials of behavioral treatment programs for urologic symptoms conducted by the investigators in which early termination was < 15% over similar time periods [36, 37].

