Aim 1/Hypothesis 1: *Compared to control, participants assigned to the integrated nocturia and insomnia behavioral intervention will demonstrate a greater reduction in nocturia frequency over 4 months*. The primary outcome of nocturia frequency will be measured as the average episodes per night at baseline, 1 week after intervention (approximately 2 months), and 4 months through the ICIQ-OAB questionnaire’s nocturia item. An LMM will be used to evaluate the group difference over time in average nocturia frequency per night, with group (the integrated intervention vs. control), time, time*group interaction, and stratified randomization variables (study site and sex) in fixed effects, and nested two-level random effects to account for correlations due to clustering by study site and participants. The time*group interaction will provide the estimated ITT effect of the integrated intervention on nocturia frequency over time. Imbalanced baseline variables, if any will be included in the LMM.

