#### Secondary comparative analyses

Aim 2/Hypothesis 2: *Compared to control, participants assigned to integrated nocturia and insomnia behavioral intervention will have greater reduction in self-reported wake after sleep onset and Insomnia Severity Index over the 4-month follow-up period*. Secondary outcomes, patient-reported wake after sleep onset and ISI, will be modeled similarly with a (G)LMM in the original scale or transformed scale as appropriate, where group, time, time*group interaction, and stratified randomization variables (study site and sex) will be included in fixed effects, and random effects will be included for nested clustering by site and participant to account for correlations due to clustering. If the distributions of the secondary outcomes are skewed and no good transformation is found, the outcomes will be categorized into categories based on quantiles or clinically meaningful values and then modeled with GLMMs using cumulative logit or generalized logit link for multinomial data. Similar fixed and random effects will be included in GLMMs. Due to the exploratory feature, no adjustment will be made for the multiple comparisons, but results will be presented as secondary outcome analyses. Secondary analyses similar to those proposed in Aim 1 will be performed on the secondary outcomes of patient-reported wake after sleep onset and ISI.

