## Discussion

This multi-site trial is designed to provide rigorous evidence to evaluate the impact of the integrated behavioral treatment for older adults with overlapping nocturia and insomnia symptoms. It will yield an integrated bladder-sleep diary that can be used to assess patients with nocturia and insomnia symptoms. In addition, the intervention will be delivered by staff from different clinical backgrounds (clinical psychologists, nurse practitioners, physician assistants) to inform future implementation efforts.

With the enrollment sites based at two VA medical centers (one in Los Angeles and one in Atlanta), recruitment sites inclusive of VA and academic medical centers, and the data coordinating center based at an academic UCSF site, this project demonstrates extensive collaboration among federal, state, and private entities to tackle nocturia, a prevalent but undertreated condition that impacts the quality of life of many older adults. The funding (grant from NIH/NIA and in-kind support from the VA Geriatric Research, Education and Clinical Centers) also reflects collaborative effort from different federal agencies. The elaborate and extensive protocol that enables multiple organizations to participate in the multi-site trial was made possible by the NIA planning grant [67]. Furthermore, the collaboration among the sites provides the opportunity to expand recruitment efforts (e.g., to academic medical centers) if the teams experience challenges in recruitment overall or in recruiting women at the VA medical centers. The NIA’s CROMS system provides close oversight of the recruitment process.

Collaboration among the two VA Geriatric Research, Education and Clinical Centers that has enabled sharing of resources and more efficient recruitment (e.g., data analyst conducting data extractions for both Los Angeles and Atlanta). The option to deliver the interventions through video encounters using the VA’s video visits and the collaboration among the VA medical centers across the federal health system is also enabling interventionists at either site to conduct the intervention visits, which provides more flexible appointment times for participants during intervention.

Future plans include a multi-center implementation trial that is informed by patients, caregivers, and other stakeholders to assess the clinical effectiveness of the integrated program among patients recruited from a variety of healthcare systems.

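### The models and the power calculation leave out clustering by interventionist, so standard errors may be too small and power may be overstated

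*Protocol article*

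**What the plan says.** The section on the choice of comparators says that both programs are "to be delivered entirely (all sessions) by a single interventionist". The control arm is delivered in the same way: "The interventionist provides a health education curriculum". There is more than one interventionist, because the Discussion says that "the intervention will be delivered by staff from different clinical backgrounds" (psychologists, nurse practitioners, physician assistants). It adds that video delivery is "enabling interventionists at either site to conduct the intervention visits".

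The primary model (Primary comparative analyses, Aim 1) has fixed effects for group, time, their interaction, site and sex, plus "nested two-level random effects to account for correlations due to clustering by study site and participants". The treatment effect is the time-by-group interaction, with baseline as one of the three modelled time points. For the secondary outcomes, "random effects will be included for nested clustering by site and participant". The exploratory outcomes follow the same pattern.

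The Sample size section bases its power on that model ("Using an approximation of the covariance matrix of the regression coefficients of the proposed linear mixed effects models (LMMs") and reports more than 80% power for "a sample of 192 participants, randomized in equal proportions to the two arms". It mentions no interventionist ICC or design effect.

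**The concern.** Delivery creates one level of clustering, the interventionist, and the model names two other levels instead. Participants who share an interventionist may have correlated outcomes after treatment, the more so because the interventionists are chosen to differ in training. Site cannot stand in for interventionist, since interventionists may treat participants of either site. The site random effect itself does little: there are only two sites, and site is already a fixed effect in the same model.

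At stake are the width of the confidence interval, the true size of the 5% test and the power claim. The first two do not depend on whether the trial has spare power.

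**Working it through.** **Inputs from the protocol article (Sample size).** 192 participants, 1:1, so 96 per arm; loss below 15%, taken as 15%, so n = 96 × 0.85 = 81.6 per arm; two-sided 5%; difference 0.7 episodes per night. No SD figure is given, but the difference is said to exceed half an SD, so SD < 0.7/0.5 = 1.4.

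**Assumptions (not in the article).** Number of interventionists, ICC, nested in or crossed with arm, and within-person correlation.

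**1. The plan's own figure.** Power = Φ(0.7/SE − 1.96), with SE = SD·√(2/n). At SD 1.4, SE = 1.4 × √(2/81.6) = 0.219, and 0.7/0.219 − 1.96 = 1.23, giving 89%. At SD 1.2 power is 96% and at SD 1.0 it is 99%. It falls to 80% at an SD of about 1.60. The claim of more than 80% therefore agrees with the article's own effect size when there is no clustering. It can be checked only as a bound.

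**2. Interventionists nested in arm, 4 per arm.** Caseload m = 81.6/4 = 20.4. Design effect DE = 1 + 19.4 × ICC. True type I error of an analysis that ignores clustering = 2[1 − Φ(1.96/√DE)]. Power uses n/DE per arm.

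| ICC | DE | Type I error | Power, SD 1.4 (d = 0.5) | Power, SD 1.2 | Power, SD 1.0 |
|---|---|---|---|---|---|
| 0 | 1.00 | 5% | 89% | 96% | 99% |
| 0.01 | 1.19 | 7% | 83% | 93% | 98% |
| 0.02 | 1.39 | 10% | 77% | 88% | 97% |
| 0.05 | 1.97 | 16% | 62% | 76% | 89% |

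The largest ICC that keeps 80% power is about 0.015 at SD 1.4, 0.040 at SD 1.2 and 0.080 at SD 1.0. With 6 per arm and ICC 0.02, type I error is 8% and power at SD 1.4 is 81%.

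**3. Small-sample degrees of freedom.** With 4 per arm nested, about 2 × 4 − 2 = 6 degrees of freedom support the comparison. Noncentral-t power at d = 0.5 is then about 69%/62%/48% for the three ICCs, and at SD 1.0 about 92%/88%/76%.

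**4. Interventionists crossed with arm.** Let K be the number of interventionists, each delivering both programs, and θ the arm-specific share of their variance. Var(difference) = 2·SD²·(1 − ICC)/n + 2·SD²·ICC·θ/K. With K = 6, ICC 0.05 and SD 1.4:

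- θ = 0: power 91%, and the SE that ignores clustering is slightly too large (true/naive 0.975).
- θ = 0.5: power 80% (ratio 1.14).
- θ = 1: power 71% (ratio 1.28).

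**5. Which interventionist term matters.** The estimate is a between-arm contrast of change from baseline. For complete data, with within-person correlation ρ and interventionists nested, Var = 2·[2·SD²(1 − ρ)]/n + 2τ²/k. Here k is the number per arm and τ² = ICC·SD² is the variance of an effect that acts only after baseline. An intercept that is the same at every visit drops out of the change and adds nothing. With SD 1.4, ρ = 0.5, n = 81.6 and k = 4:

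- No interventionist variance, or a time-constant intercept at any ICC: √(2 × 1.96/81.6) = 0.219.
- Post-baseline effect, ICC 0.02 (τ² = 0.0392): √(0.0480 + 0.0196) = 0.260.
- Post-baseline effect, ICC 0.05 (τ² = 0.098): √(0.0480 + 0.0490) = 0.312.

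**The case against.** A reader might infer that the standard errors are too small and that the power is overstated, as established facts. The article does not support that. It would need a positive ICC, few interventionists, and either nesting in arm or arm-specific variance, and none of these is stated. The text leaves crossed delivery open: interventionists are trained in the intervention protocols in the plural, and no separate control-arm team is described. If they are crossed with no arm-specific variance, the SE that ignores clustering is not too small.

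Nor is the power claim shown to be false. The article calls its effect more than half an SD and its loss less than 15%, so d = 0.5 with 81.6 per arm is the unfavourable end of its own assumptions. Several of the clustered scenarios still exceed 80%. The structured format and fidelity ratings should also limit variation between interventionists, and their number and caseload are details that an article may leave to the full plan.

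All of this stands as a limit on size and certainty. It does not remove the point. The article spells out its clustering levels and omits this one, and the inflation of the type I error in step 2 does not depend on the SD. Crossing helps only so far as interventionists do not differ in how well they deliver the active program. Staff from urology and from sleep psychology could plausibly differ more in that than in delivering a health-education curriculum.

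**Conclusion.** The point holds as a possibility that the plan should close. The stated models and the power derived from them omit interventionist clustering, and site does not absorb it. In the nested, 4-per-arm case the nominal 5% test could run at about 7% to 16%, with large-sample power of 83% to 62% at d = 0.5 for ICC 0.01 to 0.05. The effect is small or absent if the SD is near 1.0 (for power), the ICC is very small, there are many interventionists, or they are crossed with arm without arm-specific variance. All ICCs and interventionist numbers here are assumptions.

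**What to change.** - Record the interventionist for every participant in both arms. State how many there are and whether they are nested in or crossed with arm.
- Keep site as a fixed effect and drop the two-level site random effect, which is redundant.
- In the primary model, or at least in a prespecified sensitivity analysis, add an interventionist effect on the post-baseline outcomes (interventionist-by-time, zero at baseline). Make it arm-specific where interventionists deliver both programs. A simple random intercept is the obvious remedy, but it cancels from the time-by-group contrast and would leave the interval unchanged.
- Use small-sample degrees of freedom, such as Kenward-Roger.
- In the Sample size section, say that the power assumes no interventionist clustering, and show it over a range of ICCs and numbers of interventionists.

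The cost is one recorded variable and a somewhat more complex model. Intervals become wider and the power figure less favourable, markedly so if interventionists are few and nested in arm (step 3). A variance estimated from a handful of interventionists will also be imprecise, which is a reason to accept the sensitivity analysis as the minimum. Recruitment is expected to run to June 2028, so the change can be made before the final analysis.
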